## Abstract

**Background:**

Urinary retention is a common complication of spinal cord injury (SCI), which can seriously affect the quality of life of patients. Function magnetic stimulation (FMS) has been widely used in the recovery of neurological function in various diseases, but its application in urinary retention after SCI remains unclear. Therefore, we would like to conduct a pilot randomized controlled trial (RCT) to observe the feasible effect of FMS on urinary retention after SCI, to explore its mechanism of action.

**Method/design:**

This is a single-center pilot RCT, which 60 patients with urinary retention after SCI will be selected, numbered in chronological order of hospitalization, and randomly divided into 4 groups using the random number table method, Groups A (control group), Group B, Group C, and Group D; Each group will receive the same conventional rehabilitation treatment. The whole intervention period 2 weeks and will be evaluated before and after treatment to collect data on residual bladder volume, functional near-infrared spectroscopy (fNIRS), changes in voiding condition, changes in surface electromyography (SEMG) values of pelvic floor muscle and quality of life scores (QoL).

**Study hypothesis:**

We hypothesized that FMS for the treatment of urinary retention after SCI would have a significant clinical feasible effect;and that peripheral combined with central FMS would be more effective than single-site FMS for the treatment of urinary retention after SCI.

**Objective:**

(1) To illustrate the clinical effectiveness of FMS in the treatment of urinary retention after SCI and to provide a new treatment modality for the patients; (2) Comparison of the differences in the efficacy of central and peripheral single FMS and combined central and peripheral FMS in the treatment of urinary retention after SCI; (3) To explore the central control mechanisms of bladder function recovery after SCI in conjunction with changes in fNIRS.

**Trial registration:**

This study has been ethically approved by the Scientific and Ethics Committee of the First Affiliated Hospital of Gannan Medical university with approval number (LLSC-2022112401). It has been registered with the China Clinical Trials Registry with the registration number: ChiCTR2200067143.

## Introduction

### Background and rationale

Spinal Cord Injury (SCI) is a serious and disabling disease. The global prevalence of SCI is 27.04 million, with an incidence rate of 130 per 100,000, and the incidence of SCI is increasing (1, 2). More than 80% of patients with SCI have varying degrees of bladder dysfunction (3). Urinary retention is a common complication after SCI and is characterized, by bladder distension, inability to urinate or frequent urination, feeling of incomplete urination, lower abdominal distension and discomfort. It is easy to cause urinary tract infection, hydronephrosis and even life-threatening renal failure, which brings great inconvenience to the daily life of patients with SCI and seriously reduces the quality of life (4, 5).

At present, domestic and international treatments for urinary retention after SCI mainly include catheterization, medication, surgery, traditional rehabilitation training, electrical stimulation and so on (6). Among them, long-term indwelling catheterization is prone to urinary tract infection, urethral injury, and bladder atrophy (7); Long-term drug treatment leads to drug resistance in some patients and more adverse drug reactions; surgical treatment may lead to disorders of bowel fluid secretion, urinary incontinence, postoperative incision infection (8, 9); Traditional rehabilitation training has inconsistent results and variable treatment effects (10); Electrical stimulation carries the risk of discomfort and accidental injury (11). These treatments are not ideal, therefore, there is an urgent need to find a new treatment to further improve the clinical efficacy of patients with urinary retention after SCI.

Function magnetic stimulation (FMS) is a kind of treatment that generates a magnetic field through a coil, which further generates an induced electric field to depolarize the nerve tissue, so as to stimulate the nerve or muscle and produce an excitatory or inhibitory neuromuscular effect. It has the advantages of being painless, noninvasive, simple and easy to use, and is currently used clinically to treat psychological disorders, stroke, and SCI at present (12, 13). With the development of FMS therapy in recent years, many researchers have applied FMS therapy to urinary retention after SCI and reported positive clinical outcomes (14). According to the functional application of FMS, it is currently divided into peripheral FMS and central FMS, and the commonly used stimulation mode is repetitive function magnetic stimulation (rFMS). When rFMS is applied to a peripheral nerve or muscle, it is called repetitive peripheral magnetic stimulation (rPMS). When rFMS is applied to the cortex, it is known as repetitive transcranial magnetic stimulation (rTMS). Common used peripheral sites include sacral nerve roots, pelvic floor perineum, suprapubic bladder area, etc. Among them, stimulation of S3 nerve roots is more common (15, 16). Sacral nerve root MS can induce contraction of both the urethral and pelvic floor muscles, thus facilitating the production of urine flow; when the stimulation stops, the transverse urethral sphincter will relax immediately, while the urethral muscle is still markedly tense, and the pressure difference between the bladder and the urethra allows the urine to be discharged (17). Sacral nerve root MS excites contraction of the urethral muscle due to delayed activation of the spinal micturition reflex pathway, which excites the parasympathetic nerves and induces micturition (17). MS of the sacral nerve roots also activates peripheral afferent nerve fibers to enhance sensory input to the spinal cord, increasing the excitability of the descending corticospinal tracts and further inducing contraction of the urethral muscles (18). Rodic et al. (19) showed that high frequency rMS of S3 nerve roots could promote the contraction of bladder force muscle in patients with urinary retention, increase bladder pressure, and promote urination. At present, the central stimulation target is the primary motor cortex (M1), High-frequency FMS stimulation of the M1 region can activate the pontine micturition center (PMC), the neural nucleus associated with micturition found in the subcortical structures of the cerebral cortex, to enhance the activity of the urethral muscles, promote bladder contraction, and induce voluntary voiding (20). At the same time, rFMS can induce and enhance the neural conduction of other subcortical regions through stimulation of the M1 region, so that the patient can perceive the filling of the bladder, and thus can independently control the voiding reflex to maintain an effective storage and voiding state (21). Cortical high-frequency rFMS can also effectively promote the pubic-anal reflex in patients with incomplete spinal cord injury, improve the function of pelvic floor sphincter (22), strengthen the contraction of pelvic floor muscles, and improve the ability of urinary control.And the L5 layer neurons in M1 region are closely related to urination behavior. Activation of L5 neurons in M1 region will trigger bladder contraction and urination. Therefore, MS in the M1 region of the cortex can not only activate L5 neurons in the M1 region, but also use its remote effects to regulate PMC, thereby improving urination function and improving the quality of life of patients (23–25).

In the past few decades, with the development of imaging techniques, it has been possible to obtain imaging data on brain function by measuring metabolic function and blood flow changes in cortical areas that indirectly reflect local neural activity. Studies showed that vertebral cells in the primary motor cortex (M1) undergo different levels of trophic death determined by the segment and type of injury, which altered the response of the motor cortex to stimuli above the focal segment, resulting in changes in the cortical network, leading to a series of structural and functional alterations of the brain tissues controlling and transmitting neural signals, (26, 27) that is, changes in brain plasticity. Functional magnetic resonance imaging (MRI), with its advantages of non-invasive and repeatability, can continuously observe the plasticity of brain function in patients with SCI and provide imaging basis for clinical treatment. Previous studies on brain functional imaging techniques of SCI and urination dysfunction have shown (28, 29) increased neuronal activation in the bilateral primary motor cortex (M1), primary sensory cortex (S1), auxiliary motor area (SMA), paracentral lobule and other areas after SCI. The higher center of urination reflex involves many brain regions, including pons, periaqueductal gray matter, thalamus, prefrontal cortex, cingulate cortex, auxiliary motor area. Due to the limitations of research methods and conditions, the imaging studies of brain-bladder regulation are still in the initial stage.Near infrared functional brain imaging, also known as functional near-infrared spectroscopy (fNIRS), is a new type of functional brain imaging technology based on the neurovascular coupling mechanism, using the optical principle to detect the spectral changes caused by hemoglobin. fNIRS has the advantages of low cost, portability, high interference resistance, and high temporal resolution (30). fNIRS has been gradually, applied to hypothesize the mechanism of bladder control center (28), Because of its ability to easily detect changes in brain function after treatment, it can further guide neuromodulation therapy of neurogenic bladder according to the relevant indicators such as electrophysiology of the bladder, bladder capacity.

There is a lack of studies comparing the advantages and disadvantages of the effects of central and peripheral FMS for the treatment of urinary retention after SCI, and the effects of central combined with peripheral FMS for the treatment of urinary retention after SCI have rarely been studied. Therefore, the aim of this study is to compare the feasible effects of central and peripheral FMS in the treatment of urinary retention after SCI and to explore its mechanism of action and to provide reference for the clinical treatment of patients with urinary retention after SCI.

## Methods and study design

### Study design

This trial is a pilot single-center, prospective, double-blind, randomized, controlled study (e.g., Figure 1), and 60 patients with urinary retention after SCI will be selected. According to the sequence of hospitalization time, patients will be randomly assigned to group A (sham stimulation), group B (rTMS of Bilateral M1), group C (rMS of S3 nerve root), and group D (rTMS of Bilateral M1 + rMS of S3 nerve root) in a 1:1:1:1 ratio, combined with conventional rehabilitation treatment.The intervention measureswill be once a day, 20 min, 5 times a week, and the whole experiment cycle will last 2 weeks (10 times in total). Study time point: bladder residual urine volume, brain fNIRS, urination diary, pelvic floor surface electromyography Glazer assessment and quality of life (QoL) assessment will be performed 1 day before treatment and 2 weeks after treatment, respectively. A flowchart overview of the study is presented in Figure 1.

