### Sample size calculation

According to published literature (33) the mean post-intervention residual urine volume in the four groups A, B, C, and D were expected to be 302.6, 56, 107.2, and 179, respectively, with a standard deviation of 160.4. The degree of certainty 1−β = 0.90, test level *α* = 0.05, group A:B:C:D = 1:1:1:1 and sample size estimation will be performed using PASS 15 software according to the following equation.

$$n=\Psi^{2}\left[\overset{k}{\underset{i=1}{\sum }}{s_{i}}^{2}/k\right]/\left[\overset{k}{\underset{i=1}{\sum }}{\left({\bar{X}}_{i}-\bar{X}\right)}^{2}/\left(k-1\right)\right]$$

According to the predefined parameters, the minimum required samples for groups A, B, C and D were all 12 cases after the calculation of residual urine volume using One-Way Analysis of Variance F-Tests under the Means menu of PASS 15 software. Considering the lost rate of 20%, it is expected that 15 cases will be included in groups A, B, C, and D in this study, and a total of 60 cases will be included, which can ensure the accuracy and scientific accuracy of the study results.

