### Statistical analysis

All data will beanalyzed using SPSS 21.0 statistical software. The measures will beexpressed as mean ± standard deviation (
$\bar{x}$
±SD), and one-way analysis of variance (ANOVA) or chi-square test will be used in all demographic characteristics and baseline assessments, The primary and secondary outcome measures will be expressed as 
$\bar{x}$
±SD, and the data will be tested for a normal distribution. Before and after treatment, the uniformity of variance data between the two groups will be analyzed using *t* test. If the data is skewed, it will be converted to normal distribution according to the data distribution type; If the data does not conform to any distribution law, the rank sum test will be used to test the hypothesis of the data. Data with abnormal distributions or uneven variances will be analyzed using Wilcoxon rank sum tests. *X*^
**2**
^ test was used for counting data, and *p* < 0.05 for all tests was considered statistically significant.

The fNIRS data will beprocessed by professional data analysts of Wuhan Ired Medical Equipment Co., LTD. SPSS 21.0 will beused for data analysis to calculate the differences in activation intensity of each brain region, and the average concentration changes of HbO2, HbR, and HbT in each channel of subjects in each group will becalculated. Paired sample *t* test will beused to investigate the differences in blood oxygen changes before and after treatment, and one-way analysis of variance will be used for comparison between groups. *p* ≤ 0.05 will beconsidered as a statistically significant difference.

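### The outcome analysis uses two-group tests in a four-arm trial sized on a four-group F-test, and no comparison is tied to either hypothesis

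*Protocol article*

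**What the plan says.** All references are to the protocol article.

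- **Design (Study design).** Four arms, 1:1:1:1: A is sham, B is bilateral M1, and the remaining two are "group C (rMS of S3 nerve root), and group D (rTMS of Bilateral M1 + rMS of S3 nerve root").
- **Hypothesis 1 (Abstract, Study hypothesis).** It concerns stimulation as such: "We hypothesized that FMS for the treatment of urinary retention after SCI would have a significant clinical feasible effect".
- **Hypothesis 2 (same place).** "peripheral combined with central FMS would be more effective than single-site FMS". Objective 2 asks for "Comparison of the differences in the efficacy of central and peripheral single FMS and combined central and peripheral FMS".
- **Sizing (Sample size calculation).** Post-treatment residual urine means "were expected to be 302.6, 56, 107.2, and 179, respectively, with a standard deviation of 160.4", with 90% power and alpha 0.05, "using One-Way Analysis of Variance F-Tests under the Means menu of PASS 15 software". The result is 12 per arm, raised to 15 for 20% loss.
- **Outcome analysis (Statistical analysis).** "Before and after treatment, the uniformity of variance data between the two groups will be analyzed using" a t test, with rank-sum tests where normality or equal variance fails, and p < 0.05 for every test. One-way ANOVA is named for demographic and baseline data and for comparing groups on fNIRS. It is not named for residual urine.

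**The concern.** Three parts of the plan do not fit together. The design has four arms, the sample size rests on one F-test across all four, and the outcome tests are for two groups. Nothing says which two groups are meant or which hypothesis a given test answers.

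At stake is what a significant result would mean. With six possible pairs, each at 0.05, a claim that stimulation works could rest on whichever arm happened to beat sham. Falling back on the F-test used for sizing does not repair this. That test asks whether any of the four means differ, so a difference between B and D alone can produce a rejection.

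**Working it through.** **Inputs.** Means A 302.6, B 56, C 107.2, D 179; SD 160.4; alpha 0.05; 12 per arm (all from Sample size calculation). Assumptions: the unit is mL, contrasts are two-sided, and data are normal with a common SD.

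**1. Reproduce the plan's figure.** The grand mean is 161.2. The sum of squared deviations is 141.4² + 105.2² + 54.0² + 17.8² = 34,293.84. The noncentrality is 12 × 34,293.84 / 160.4² = 16.0, with 3 and 44 df. Power is 0.910 at 12 per arm and 0.879 at 11, so 12 is right. Then 12 / 0.80 = 15 per arm, 60 in total. The sample size reproduces for the F-test.

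**2. Does the F-test answer hypothesis 1?** Keep the planned active means and set sham to their average, (56 + 107.2 + 179)/3 = 114.07. Stimulation then has no average benefit over sham. The noncentrality is 3.56, and the F-test rejects with probability 0.297 at 12 per arm (0.371 at 15). This is not a type I error of the F-test, since the arms do differ. It shows that rejection is not evidence for hypothesis 1. The sham mean of 114.07 is chosen for illustration.

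**3. Do pairwise tests answer it?** With all four means equal, I simulated 200,000 trials at 12 per arm and ran two-sample t tests at 0.05.

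| Family | Chance of at least one p < 0.05 |
|---|---|
| Three comparisons with sham | 12.5% |
| All six pairs | 20.3% |

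The results are practically the same at 15 per arm. If the tests were independent, the figures would be 1 − 0.95³ = 14.3% and 1 − 0.95⁶ = 26.5%. They are lower here because the comparisons share arms.

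**4. A single contrast for hypothesis 1.** Mean of B, C and D minus A: 114.07 − 302.6 = −188.5. SE = 160.4 × √(1/12 + 1/36) = 53.5. Power is 93% with 44 df. At 15 per arm the SE is 47.8 and power is 97%.

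**5. Contrasts for hypothesis 2.** SE of a pair = 160.4 × √(2/12) = 65.5. On the planning means D − B = +123.0 and D − C = +71.8. Positive values mean more residual urine with the combination, the reverse of hypothesis 2. The power to declare these differences is 45% and 19%.

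**6. Factorial quantities.**

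| Quantity (12 per arm, 44 df) | Value | SE | Power |
|---|---|---|---|
| Interaction, D − B − C + A | +318.4 | 92.6 | 92% |
| M1 main effect, (B + D)/2 − (A + C)/2 | −87.4 | 46.3 | 45% |
| S3 main effect, (C + D)/2 − (A + B)/2 | −36.2 | 46.3 | 12% |
| B − A | −246.6 | 65.5 | 96% |
| C − A | −195.4 | 65.5 | 83% |

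On these means M1 changes residual urine by 56 − 302.6 = −246.6 without S3 and by 179 − 107.2 = +71.8 with S3. A main effect averages the two.

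**The case against.** **Contrasts may be left to the analysis plan.** An article condenses, and naming contrasts is often done elsewhere. That would excuse silence. Here the article does state a method for the outcomes, and the method fits neither the four arms nor the test used for sizing. The finding is about what is stated.

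**Pairwise tests do compare stimulation with sham.** This stands. A reader might infer that nothing in the plan tests stimulation against sham, and that goes too far: B, C and D could each be compared with A. The defect is that these comparisons are neither named, tied to a hypothesis nor adjusted.

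**The pooled average is only one reading of hypothesis 1.** This also stands, and such an average can hide one ineffective arm. It is still a single test of the claim as worded, and the arm-level estimates can be shown with it.

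**The factorial argument.** The arms look like a 2×2, so a reader might infer that pairwise analysis wastes half the information on each site, or that hypothesis 2 needs an interaction test. The documents support neither. A gain from pooling over the other site requires roughly additive effects, and the planning means imply opposite ones: on those means the half-sample comparisons with sham have far more power than the all-patient main effects. Hypothesis 2 as worded is D against B and D against C. The article never calls the design factorial. Its Research group and intervention section describes sham at the head only, so A is not a sham control for sacral stimulation and the 2×2 is not clean.

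**Conclusion.** The concern holds in a limited form. The stated outcome tests do not match a four-arm trial or its sizing test, and neither hypothesis has a named comparison. Read as pairwise tests at 0.05, hypothesis 1 carries about a 12% chance of at least one false positive against sham, and about 20% if all six pairs are used. The sizing F-test cannot stand in, because it can reject with no average benefit over sham.

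The false-positive figures assume normal data, equal variances and pairwise use of the stated tests. The quoted sentence is garbled and could also be read as a before-after comparison or a check of variances; on those readings too, no between-arm test is tied to a hypothesis. The power figures rest on the article's own planning means and SD. The sample size of 12 (15 with loss) is arithmetically right for the F-test and is not in dispute.

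This should be corrected before analysis. It does not invalidate the design.

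**What to change.** In Statistical analysis, replace the two-group wording for residual urine with one linear model containing all four arms. It has the same fit and overall F as the one-way ANOVA used for sizing. Name in advance:

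1. **Hypothesis 1:** the mean of B, C and D minus A, as the single test, with the three arm-versus-sham estimates and 95% CIs beside it.
2. **Hypothesis 2:** D − B and D − C, with a stated multiplicity rule (for example, tested only after hypothesis 1 succeeds, with both required for the claim).
3. **Supportive:** the M1 by S3 interaction with its 95% CI, as a description of how the sites combine. Note beside it that sham is described at the head only. Do not rest conclusions on all-patient M1 or S3 main effects.

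Before quoting any power for hypothesis 2, reconcile the planning means, which place D above both B and C, with the direction of that hypothesis.

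The cost is analysis wording, with no extra patients or visits. The downside is that the pooled contrast can mask one ineffective arm, which is why the arm-level estimates must accompany it.

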**Figure 1 fig1:**
[figure not shown]
Study design. SCI, spinal cord injury; rMS, repeated magnetic stimulation; BR, bladder residual urine; fNIRS, functional near-infrared spectroscopy; QoL, quality of life.

This study will obey the Standard Protocol Items: recommendations for Interventional Trial (SPIRIT) guidelines (31). Each participant in this study will sign an informed consent form (Supplementary material) prior to participation. All participants will be informed of the nature of the trial, the purpose and procedure involved, the expected completion time, potential adverse reactions and possible benefits.

### Ethics and dissemination

This study was approved by the Science and Ethics Committee of the First Affiliated Hospital of Gannan Medical University on November 30, 2022 (Approval number LLSC-2022112401), and has been registered in the Chinese Clinical Trial Registry (registration no. ChiCTR2200067143, https://www.chictr.org.cn/index.html).

## Eligibility criteria

### Inclusion criteria

Participants who met all of the following criteria willbe considered for inclusion: (1) met the classification criteria for SCI in the International Standard for Neurological Classification of SCI (32) and were confirmed by MRI or CT; (2) clinically present with varying degrees of urinary retention, i.e., residual urine volume > 100 mL after bladder emptying; (3) aged 18–60 years, regardless of gender; (4) patients graded B, C, or D according to the American Spinal Cord Injury Association functional rating criteria (ASIA); (5) had a disease duration between 1 month and 2 years and underwent intermittent catheterization; and (6) voluntarily participatingin this study and signingan informed consent form.

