### Randomization and blinding

Randomization of included patients based on length of stay will be performed using the random number table method. Throughout the study, all investigators and subjects will be unaware of the allocation of interventions, Outcome evaluators and data analysts will be blinded, and subjects will be randomly assigned to groups by persons unrelated to the trial. Opaque closed envelopes containing sequence numbers used for allocation concealment will be identified with different numbers. Once the sequences is generated, the envelopes will be placed in a secure place in numerical order and the paper containing the corresponding group information will be placed in the envelopes. Sequence generation and production will be performed by rehabilitation physicians not involved in this study.

An experienced blinding rehabilitation physician or therapist will perform an initial assessment of enrolled patients and an assessment after 2 weeks of treatment. In the event of a serious adverse event, emergency unblinding will be performed and the involved subject will be removed from the trial protocol. When the experiment is complete, the statisticians will have four sets of data.

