## Limitations

Despite the above advantages of this study, there are still some limitations. First, the patients we included were only with urinary retention after SCI, so our conclusions are only applicable to patients with urinary retention after SCI. Second, due to the lack of professional evaluation of patients’ psychological state, the influence of psychological state on the therapeutic effect is neglected. In addition, the inclusion of subjects in this study was strictly controlled, but the heterogeneity of patients in the course of experimental intervention should still be taken into account, such as the different dose of drug intervention and the different speed of nerve recovery in patients of different ages. Nevertheless, heterogeneity was similar across conditions due to the use of randomized controlled designs.

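### The protocol says randomisation made patient heterogeneity similar across arms, but four unstratified arms of 15 do not ensure this and the stated comparisons are unadjusted

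*Protocol article*

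**What the plan says.** Under Inclusion criteria, an eligible patient "had a disease duration between 1 month and 2 years and underwent intermittent catheterization", and grades B, C and D on the ASIA scale are all admitted.

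Allocation is described in the Abstract, under Study design and under Randomization and blinding. The last of these says: "Randomization of included patients based on length of stay will be performed using the random number table method". Read with the other two, length of stay here is the order in which patients are numbered on admission. It is not time since injury and it is not a stratum. No stratification factor is named in any of the three places.

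Statistical analysis lists t tests, rank sum tests, chi-square tests and one-way ANOVA. Baseline characteristics are to be compared across arms, but no outcome comparison carries a covariate.

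Limitations concedes heterogeneity, giving as examples "the different dose of drug intervention and the different speed of nerve recovery in patients of different ages", and then closes the matter: "Nevertheless, heterogeneity was similar across conditions due to the use of randomized controlled designs".

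**The concern.** The closing sentence of Limitations credits the design with a property it does not have. Randomisation makes the arms comparable on average over repeated trials. It does not make them similar in one trial with 15 patients per arm. The sentence is also in the past tense, as an established fact, in a plan for a trial still to be run.

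The entry criteria leave room for the arms to differ. Time since injury spans a 24-fold range (1 to 24 months) and severity spans three grades. If either factor predicts the change in residual urine over the 2 weeks, two things follow. A chance imbalance would move an arm contrast, and the unexplained variation would widen every interval. The second objective, comparing central, peripheral and combined stimulation, is the most exposed, because the planned differences among the active arms are the small ones. Both factors are established at screening, so the design and analysis can use them at little cost.

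**Working it through.** **Inputs from the protocol article (Sample size calculation).** Expected residual urine: A 302.6, B 56, C 107.2, D 179 mL; SD 160.4 mL; α 0.05; power 0.90; 12 evaluable per arm; 20% loss; 15 per arm, 60 in total.

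**Assumptions, not in the documents.** 30% to 50% of patients are in an early-recovery phase. Early patients fall by 50 to 150 mL more than late ones over the study.

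**1. The plan's own figure.** The grand mean is 161.2 and the sum of squared deviations is 34,293.84. The noncentrality is λ = n × 34,293.84 / 160.4². At n = 11, λ = 14.66 and power is 0.879. At n = 12, λ = 16.00 and power is 0.910. So 12 per arm reproduces, and 12 / 0.8 = 15 per arm. Nothing below changes that number.

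**2. How often arms differ.** Allocate 18 or 30 early patients at random to four arms of 15 (multivariate hypergeometric, simulated with 200,000 or more draws):

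| Early patients | Some pair differs by ≥ 4 of 15 | Some pair differs by ≥ 5 of 15 | One pre-named pair differs by ≥ 5 of 15 |
|---|---|---|---|
| 18 of 60 (30%) | 51% | 28% | 7% |
| 30 of 60 (50%) | 58% | 36% | 10% |

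For a continuous factor, the standard error of the standardised difference between two arms is √(2/15) = 0.37. A gap above 0.5 SD then has probability 0.17 for one given pair and 0.52 for at least one of the six pairs.

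**3. Size of a resulting shift.** A difference of 5 of 15 is 33 percentage points. The shift is 0.33 × 50 = 17 mL to 0.33 × 150 = 50 mL.

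**4. Against the trial's own noise.** The standard error of a two-arm difference is 160.4 × √(2/n), which is 58.6 mL at n = 15 and 65.5 mL at n = 12. The shift is below one standard error throughout.

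**5. Against the planned differences.** B–C: 107.2 − 56 = 51.2 mL. C–D: 179 − 107.2 = 71.8 mL. B–D: 179 − 56 = 123 mL. A shift of 17 to 50 mL is 33% to 98% of B–C and 24% to 70% of C–D. Normal-approximation power for B–C at 12 per arm is about 0.12.

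**6. False-positive rate.** Over all allocations, the simulated type I error of the ANOVA was 0.049 to 0.051 (early/late difference of 40 to 120 mL, 50% early). Given a gap of at least 30 points in some pair, it was 0.051 to 0.071. For a two-arm t test in a pair with 10 versus 5 early patients of 15, it was about 6% at 50 mL and 10% at 150 mL.

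**7. Precision from adjustment.** A 50:50 factor worth δ mL explains R² = 0.25 δ² / 160.4², and intervals shorten by 1 − √(1 − R²). At δ = 50, R² = 0.024 and the gain is about 1%. At δ = 150, R² = 0.219 and the gain is about 12%.

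**The case against.** The case on the other side has real force.

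- **Unstratified randomisation is valid.** The p-value already allows for chance imbalance, and step 6 confirms that the unconditional error rate stays at 5%. A reader might infer that spontaneous recovery is likely to be mistaken for the effect of one stimulation site. The documents do not support that. It is a possibility after an unlucky allocation, and even then the shift is below one standard error. This stands.
- **Limitations does not name these factors.** It speaks of "the different speed of nerve recovery in patients of different ages" and of drug dose. A reader might infer that the protocol itself identifies time since injury or ASIA grade as the source of uneven recovery, but it does not. This stands. The error in the sentence remains, because it covers heterogeneity in general.
- **The documents give no recovery figures.** Nothing in them states how residual urine changes with time since injury or grade, so the early share and the mL values are assumptions. This stands.
- **The 28% to 36% figures take the worst of six pairs.** For one pre-named pair the figure is 7% to 10%. Both are given, because the protocol singles out no one pair.
- **A small single-centre pilot may forgo strata, and a fuller protocol or analysis plan may hold covariates.** Broad eligibility is no error, and silence on covariates alone would not be a finding. But the article does state its tests, all unadjusted, and no further document would make the Limitations sentence true.

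**Conclusion.** The point holds in a limited form. The Limitations sentence is wrong as written: at 15 per arm, similarity on a prognostic factor is not ensured, and under the assumed prevalence a gap of at least 33 points between some two arms occurs in roughly three trials in ten. The consequence is chance imbalance and lost precision, not systematic bias. Broad entry criteria and the absence of strata do not invalidate the trial.

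The practical weight falls on the comparisons between stimulation sites, where a shift of 17 to 50 mL is large beside planned differences of 51 and 72 mL and power is already low. The mL range rests wholly on the assumed 50 to 150 mL early/late difference. If neither factor predicts the 2-week change, the shift and the precision gain vanish and only the wording error remains. This is an inexpensive improvement worth making, not a fatal flaw.

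**What to change.** 1. Analyse post-treatment residual urine with ANCOVA, adjusting for baseline residual urine, time since injury and ASIA grade. All three are already collected at screening or baseline. Baseline residual urine belongs in the model because it is the outcome itself measured before treatment.
2. If enrolment has not begun, prepare the envelopes in two sets, split by one two-level cut of time since injury fixed beforehand, each balanced 1:1:1:1, and include that stratum in the model. The documents give no basis for a particular cut, so the investigators should choose and justify it. If enrolment has begun, leave the allocation alone and rely on adjustment.
3. Replace the last sentence of Limitations with a statement that randomisation balances prognostic factors only in expectation, that chance imbalance is possible with arms of this size, and that it is handled by adjustment.

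Cost: no extra patients, visits or measurements. Baseline urine and time since injury take one degree of freedom each, ASIA grade one or two, and the stratum one more if it is added beside continuous time. That is three to five of the 48 − 4 = 44 residual degrees of freedom at 12 per arm. Two envelope lists will leave some incomplete blocks. The gain depends on how prognostic the factors are: about 1% to 12% shorter intervals for a 50:50 early/late factor worth 50 to 150 mL, before any contribution from baseline urine or ASIA grade.
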